
**Table 1. Overall survival rates by risk group**

| Risk Group | 5-year | 10-year | 15-year |
|------------|--------|---------|---------|
| 1          | 85%    | 59%     | 39%     |
| 2          | 82%    | 50%     | 24%     |
| 3          | 68%    | 32%     | 16%     |
| 4          | 52%    | 19%     | 12%*    |

\* Extrapolated from 13-year results

**Table 2. Probability of surviving during five-year interval by risk group**

| Risk Group | 1-5 | 6-10 | 11-15 |
|------------|-----|------|-------|
| 1          | .85 | .69  | .66   |
| 2          | .82 | .61  | .48   |
| 3          | .68 | .47  | .50   |
| 4          | .52 | .37  | .63*  |

### 13.2.3 Erectile Function and Quality of Life

The International Index of Erectile Function Questionnaire (IIEF) is the primary measure for erectile function (ED). IIEF question number 1 (“How often were you able to get an erection during sexual activity?”) is scored from: none/almost never (*response 0-1*) or  $\leq$  half the time (*response 2-3*) to most times/almost always/always (*response 4-5*). A response of 0 to 3 on question number 1 of the IIEF will be considered erectile dysfunction. If the expected rate of ED at 12 months is 29%, then 688 patients per arm is sufficient for 90% statistical power and a two-sided significance level (0.05) to detect a reduction in ED to 19%. This assumes that 26% of the patients will have ED prior to the start of therapy and 80% compliance at 1 year. Only patients that respond 4-5 on question number 1 of the IIEF will be considered for this endpoint. The subset of patients age 70 and above will also be examined. Assuming 39% will have ED at 12 months, then this study will have the same statistical parameters to detect a reduction in ED to 25%, assuming that 50% of the sample is age 70 and above.

Quality of life will be measured using the Spitzer Quality of Life Index (SQLI). A 0.5 point difference in SQLI scores has been shown to be clinically meaningful, assuming a standard deviation of 0.54 for SQLI. If ED reduces quality of life, then the difference in quality of life between the arms only may occur in this subgroup. In addition, ED may cause a reduction in quality of life greater than the minimally important difference; assuming the effect is 50% greater, then a 0.75 difference is expected. However, only those patients with ED may substantially impair quality of life. Therefore, the proportion of patients with ED may reduce the observable difference in quality of life. Using the above estimates of ED and sample size, this study will have 90% statistical power to find an observable difference of 0.12 in SQLI between the two arms with a significance level of 0.05 (*two-sided*).

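### Protocol 13.2.3: the age-70+ erectile dysfunction comparison (39% v 25%) has about 84–86% power on the section's own inputs, not the 90% claimed

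*Protocol*

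**What the plan says.** Protocol Section 13.2.3 sets out the ED comparison at 12 months. The expected rate is 29% and the target 19%: "then 688 patients per arm is sufficient for 90% statistical power" with "a two-sided significance level (0.05) to detect a reduction in ED to 19" per cent. The losses are explicit: "This assumes that 26% of the patients will have ED prior to the start of therapy and 80% compliance at 1 year". The endpoint is restricted to men potent at baseline: "Only patients that respond 4-5 on question number 1 of the IIEF will be considered for this endpoint".

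The section then turns to men aged 70 and above: "Assuming 39% will have ED at 12 months", "then this study will have the same statistical parameters to detect a reduction in ED to 25" per cent, "assuming that 50% of the sample is age 70 and above". The only statistical parameters given up to that point are 90% power and a two-sided 0.05 level, so those are what the subgroup is said to share.

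Section 13.4.4 plans a chi-square test for the one-year ED comparison, and further comparisons in subsets that include age below 70 v 70 and over.

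**The concern.** Halving the sample while moving from a 10-point difference (29% v 19%) to a 14-point difference (39% v 25%) keeps the power only if the larger difference fully offsets the smaller number and the larger variance at rates nearer 50%. The section shows no calculation for this. The power statement is attached to an age comparison that Section 13.4.4 plans. If the true power is lower, the chance of missing the target effect in older men is higher than the stated 10%, and a null result there would carry less weight than the protocol implies.

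The section also gives an age-specific ED rate at 12 months but no age-specific baseline rate. The only baseline figure available for the subgroup is the all-age 26%.

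**Working it through.** **Inputs, all from Section 13.2.3 unless noted**
- 688 per arm; two-sided α = 0.05 (z = 1.960); 90% power (z = 1.2816)
- 26% excluded for baseline ED; 80% compliance at one year
- All ages: 29% v 19%. Age 70+: 39% v 25%, with 50% of the sample in this group
- Chi-square test (Section 13.4.4)

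**Formulas** (pooled two-proportion test, p̄ the mean of the two rates)

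- n per arm = [1.960·√(2p̄(1−p̄)) + 1.2816·√(p₁(1−p₁) + p₂(1−p₂))]² / (p₁−p₂)²
- Power = Φ{ [|p₁−p₂| − 1.960·√(2p̄(1−p̄)/n)] / √[(p₁(1−p₁) + p₂(1−p₂))/n] }
- The continuity-corrected power subtracts 1/n from |p₁−p₂|.

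**Step 1: reproduce the all-age claim**

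- Evaluable per arm = 688 × 0.74 × 0.80 = 407.3
- p̄ = 0.24. Required n = (1.960 × 0.6040 + 1.2816 × 0.5998)² / 0.10² = 381.2, or 401.0 with continuity correction
- 401 / (0.74 × 0.80) = 677 randomised per arm, close to the stated 688
- Power at 407.3: Φ[(0.10 − 0.0587)/0.0297] = Φ(1.391) = 91.8%; 90.5% corrected

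The stated figure is reproduced. This confirms that both losses were applied and that the method matches the section's.

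**Step 2: apply the same method to men aged 70 and over**

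- Evaluable per arm = 407.3 × 0.50 = 203.6
- p̄ = 0.32. Required n = (1.960 × 0.6597 + 1.2816 × 0.6522)² / 0.14² = 231.2, or 245.3 corrected (232 and 246 rounded up)
- Power at 203.6: Φ[(0.14 − 0.0906)/0.0457] = Φ(1.081) = 86.0%; 83.5% corrected

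**Step 3: other calculations at the same n**

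| Method | Power |
|---|---|
| Unpooled variance | 86.5% |
| Arcsine | 86.1% |
| Exact enumeration of chi-square (n = 204) | 86.2% |
| Exact enumeration, Yates-corrected (n = 204) | 83.8% |

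None reaches 90%.

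**Step 4: other bases for the sample** (sizes from Section 13.2.2)

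| Randomised per arm | Evaluable 70+ per arm | Power | Corrected |
|---|---|---|---|
| 688 (Section 13.2.3) | 203.6 | 86.0% | 83.5% |
| 705 (half of 1410) | 208.7 | 86.8% | 84.4% |
| 760 (half of 1520) | 225.0 | 89.2% | 87.2% |

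**Step 5: what would give 90%**

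- Randomised per arm: 232 / (0.74 × 0.80 × 0.50) = 784; corrected, 246 / 0.296 = 831
- Or a share aged 70+ of 231.2 / 407.3 = 57%; corrected, 245.3 / 407.3 = 60%
- Or, at 203.6 per arm, a fall from 39% to about 24.1%; corrected, about 23.7%

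**Step 6: sensitivity to baseline ED in men aged 70+**

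The protocol gives no age-specific baseline rate, so 35% and 45% below are assumptions.

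| Baseline ED | Evaluable per arm | Power (uncorrected) |
|---|---|---|
| 26% (stated, all ages) | 203.6 | 86.0% |
| 35% | 688 × 0.5 × 0.65 × 0.80 = 178.9 | 81% |
| 45% | 688 × 0.5 × 0.55 × 0.80 = 151.4 | 74.5% |

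**The case against.** The strongest reply is that 688 belongs to the all-age sentence, while the subgroup sentence speaks of the study and the sample as a whole. On the full accrual of 1520, uncorrected power is 89.2%, and the rate detectable with 90% power is 24.8%, which rounds to the stated 25%. This narrows the gap but does not close it. 688 is the only sample size in Section 13.2.3, the continuity-corrected figure on 1520 is still 87.2%, and 1520 includes the 8% that Section 13.2.2 allows for ineligible cases or missing data. Part of that 8% may overlap with the 20% non-compliance; the protocol does not say.

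Other readings would reach 90%, but each contradicts the text. A one-sided 0.05 test gives 90.2% even with continuity correction, but the section says two-sided. Ignoring the baseline-ED exclusion (275 per arm, 94%) or the compliance loss (255 per arm, 92.5%) also suffices, but the section imposes both.

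It is also fair to say that little depends on this. The trial is sized on 715 deaths, and the age subset has no allocated alpha, stopping rule or sample size. The inputs are round planning figures: a 57% share aged 70+, or compliance of about 91%, would restore 90% uncorrected. A null result would in any case be judged mainly by its confidence interval. These points limit the importance of the error; they do not make the stated power right.

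The baseline-ED scenarios are assumptions and do not form part of the arithmetic error. Their direction is plausible, because Section 1.7 names age and pretreatment sexual function as determinants of erectile function, but the protocol supports no particular size.

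**Conclusion.** The concern holds. On the section's own inputs (688 per arm, 26% baseline ED, 80% compliance, half aged 70+, two-sided 0.05), power for 39% v 25% is 86.0%, or 83.5% with continuity correction, against the 90% claimed. The type II error is therefore 14% to 16.5% instead of 10%, and about 204 evaluable men per arm are available where 232 to 246 are needed.

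The all-age claim is sound. The error is confined to one power statement for a subset of a secondary endpoint and changes nothing in the trial's size or primary analysis. The 84–86% range assumes that the all-age 26% baseline rate also applies to men of 70 and over; a higher rate would lower it.

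**What to change.** Replace the subgroup power statement in Section 13.2.3 with one saying that about 204 evaluable men aged 70 and over per arm give roughly 84–86% power (with and without continuity correction) to detect 39% v 25% at two-sided 0.05. Equivalently, state 90% power for a reduction from 39% to about 24%, uncorrected. Add that the figure assumes 26% baseline ED in this age group and falls if the rate is higher. If full accrual was the intended base, say so and give 89% uncorrected, 87% corrected.

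The cost is one sentence and a slightly less favourable stated power. The sample size and the planned analyses stay as they are.

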With respect to 3D-CRT and sexual function, Roach analyzed the data from RTOG 94-06 to assess the impact of dose to the penile bulb on erectile function. Using dose and volume data stored in the 3D QA center database, the dose to the penile bulb was computed retrospectively on 39 previously-potent patients treated to the 68.4 Gy and 73.8 Gy dose arms. There was a significantly higher rate of ED at 2 years ( $p=0.048$ , hazard ratio  $\sim 5.0$ ) in patients if they received a mean dose of more than 52.5 Gy to the penile bulb. In this trial, the penile bulb structure will be defined prospectively. Dose to that structure will be recorded along with all other dosimetric parameters. Given the close proximity of the penile bulb to the prostate gland, the patients in the high dose arm may receive a slightly, yet significant, higher dose to the bulb.

In a retrospective study of 287 patients diagnosed with prostate cancer in clinical stages A to C and treated with 3D-CRT to 6200 to 7380 cGy, 29% experienced ED. For patients older than 70 years, 39% experienced ED after treatment. At months 1, 20, 40, and 60, actuarial ED rates after 3D-CRT were 4%, 25%, 41%, and 47%, respectively. Factors identified as significant predictors of post-3D-CRT ED included pre-treatment ED, diabetes, coronary artery disease, and anti-androgen medication usage.

The importance of sexual functioning as a quality of life issue should not be underestimated. In a study of 413 impotent men and 109 controls, satisfaction with sexual life was found to be a powerful predictor of satisfaction with life as a whole. Further, the importance of sexual functioning as a major issue in patient decision making regarding prostate cancer treatment has been demonstrated. Quality versus quantity of life trade-offs have been documented in up to two-thirds of men with prostate cancer who are willing to accept at least a 10% decrement in survival for a treatment that offered a better chance of preserving erectile function. The long-term impact of cancer treatments also highlights the consequences of cure on quality of life. One study, which used a battery of quality-of-life instruments, concluded that cancer survivors enjoy quality of life similar to their neighbors in all but one aspect of daily life: sexual functioning.

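### The age 70+ erectile-dysfunction comparison has about 84-86% power on the section's own inputs, not the 90% carried over, and the 12-month label on 29% and 39% needs a source

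*Protocol*

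**What the plan says.** Section 13.2.3 of the protocol sets the main comparison: "If the expected rate of ED at 12 months is 29%, then 688 patients per arm is sufficient for 90% statistical power", with "a two-sided significance level (0.05) to detect a reduction in ED to 19" per cent as the contrast. The attrition is explicit: "This assumes that 26% of the patients will have ED prior to the start of therapy and 80% compliance at 1 year". The analysis set is also explicit: "Only patients that respond 4-5 on question number 1 of the IIEF will be considered for this endpoint".

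The section then turns to older men. "Assuming 39% will have ED at 12 months", it says, "this study will have the same statistical parameters to detect a reduction in ED to 25" per cent, "assuming that 50% of the sample is age 70 and above". Read plainly, the 90% power and two-sided 0.05 of the main comparison carry over to this subset. Section 13.4.4 names a chi-square test for ED at one year and plans a comparison by age below 70 against 70 or older.

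Section 13.2.3 cites no source for 29% or 39%. Both figures appear in section 1.7, for a retrospective series of 287 men treated with 3D-CRT: 29% overall and 39% in men older than 70, neither with a time point. For the same series the section reports: "At months 1, 20, 40, and 60, actuarial ED rates after 3D-CRT were 4%, 25%, 41%, and 47%, respectively".

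**The concern.** Halving the sample roughly halves the evaluable men, while the detectable difference widens only from 10 to 14 percentage points. Whether that keeps 90% power can be checked directly, because every input is stated. If it does not, the protocol promises a power for the older subset that the design does not deliver, and a null result there would be read as stronger evidence of no difference than it is.

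The second issue is the event rate. A cumulative rate cannot fall over time, so a series that reaches 25% at month 20 cannot have stood at 29% at month 12. If that series is the source, the 12-month label on the 29% is wrong, and the power is stated for a rate that does not belong to the time point analysed.

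**Working it through.** **Inputs.** From section 13.2.3: 688 per arm; 26% with ED at baseline, so 0.74 retained; 0.80 compliance; 0.50 aged 70 or more; two-sided 0.05; 90% power; 29% against 19% overall and 39% against 25% at age 70+. From section 13.4.4: chi-square test of two proportions. From section 13.2.2: 1410 patients (705 per arm) before inflation and 1520 (760 per arm) after.

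**Formulas.** With d = p1 - p2 and p̄ the mean of the two rates:

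- n per arm = [1.960 √(2p̄(1-p̄)) + 1.2816 √(p1(1-p1) + p2(1-p2))]² / d²
- power = Φ{[d√n - 1.960 √(2p̄(1-p̄))] / √(p1(1-p1) + p2(1-p2))}
- continuity correction: replace d√n by d√n - 1/√n

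**Step 1: the main statement.** Evaluable men: 688 × 0.74 × 0.80 = 407.3 per arm. For 29% against 19%, p̄ = 0.24.

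- Required n = (1.960 × 0.6040 + 1.2816 × 0.5998)² / 0.01 = 381.2, so 382 (401 corrected). That is 645 (677 corrected) randomised per arm, against 688 stated.
- Power at 407.3 = Φ[(2.0182 - 1.1838) / 0.5998] = Φ(1.391) = 91.8%; corrected 90.5%.

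The statement reproduces, so the formula and attrition factors are being read as intended.

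**Step 2: the age 70+ statement.** Evaluable men: 688 × 0.50 × 0.74 × 0.80 = 203.6 per arm. For 39% against 25%, p̄ = 0.32.

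- Required n = (1.960 × 0.6597 + 1.2816 × 0.6522)² / 0.0196 = 231.2, so 232 (246 corrected). Divided by 0.296 (0.50 × 0.74 × 0.80), that is about 784 (831 corrected) randomised per arm.
- Power at 203.6 = Φ[(1.9979 - 1.2930) / 0.6522] = Φ(1.081) = 86.0%.
- Corrected: Φ[(1.9979 - 0.0701 - 1.2930) / 0.6522] = Φ(0.973) = 83.5%.
- Exact binomial enumeration gives 86.2% and 83.8%.

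**Step 3: more generous denominators and a different target.**

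| Per arm | Evaluable, 70+ | Contrast | Power | Corrected |
|---|---|---|---|---|
| 688 | 203.6 | 39% v 25% | 86.0% | 83.5% |
| 705 | 208.7 | 39% v 25% | 86.8% | 84.4% |
| 760 | 225.0 | 39% v 25% | 89.2% | 87.2% |
| 688 | 203.6 | 39% v 24% | 90.6% | 88.6% |

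**Step 4: the 12-month label.** In the section 1.7 series the month-12 actuarial rate must lie between 4% (month 1) and 25% (month 20). The 29% used for month 12 exceeds even the month-20 value. No interpolation is needed for this. No age-specific curve is given, so the same test cannot be applied to the 39%.

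**The case against.** The case against has real force.

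- **The miss is small and the subset secondary.** The shortfall is 4 to 6.5 points in one subset of one secondary endpoint. It nearly closes at 760 per arm (89.2%), and no sample-size decision rests on it. This stands as a limit on importance. It does not make the 90% right. The 760 figure also needs all 1520 patients to be eligible with data, while section 13.2.2 adds those patients to cover up to 8% who are not.
- **A different test may lie behind the figure.** A one-sided 0.05 test with continuity correction needs 203 evaluable men, or about 686 per arm, close to 688. That may be where the figure arose, but the section states a two-sided level.
- **The source of the rates is inferred.** Section 13.2.3 cites none and words the 29% conditionally. The trial's ED definition (question 1 of the IIEF), its doses and its baseline-potent population may differ from the series, and a cumulative actuarial rate is not prevalence at one visit. This stands, so the conflict over 29% is conditional on the series being its source, and the 39% is undocumented rather than disproved.

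A reader might go further and infer that the main comparison is underpowered. Linear interpolation, 4 + 21 × 11/19, puts month 12 near 16%. The same relative reduction (to 10.5%) then has about 64% power. But that rate is an assumption, and so is the effect scale. A 10-point drop has about 99.6% power from 16% and 94.7% from 25%. A lower control rate alone does not defeat the main statement.

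A reader might also fault the section for powering only a reduction, since section 1.7 says the high-dose arm may receive more penile-bulb dose. The test is two-sided and section 13.2.3 does not assign the rates to arms, so this is not an error.

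**Conclusion.** The age 70+ power statement is wrong as written. On the section's own inputs it is about 84-86%, not 90%. This assumes that the 26% baseline ED and 80% compliance apply equally to older men and that those men divide evenly between arms. Baseline ED may well be commoner at 70+, which would lower the power further, but the protocol gives no age-specific figure, so nothing is added here for that.

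The 12-month label on 29% conflicts with section 1.7 if that series is the source, and the 39% has no documented time point. It would be too much to conclude that the section's power statements fail in general: the main 29% against 19% statement holds on its inputs. The primary survival analysis is unaffected.

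**What to change.** 1. Restate the age 70+ power as about 84-86% for 39% against 25%. Alternatively, keep about 90% and attach it to a reduction from 39% to about 24% (90.6% uncorrected, 88.6% corrected).
2. Give the source of the 29% and 39% as 12-month rates. If they come from the series in section 1.7, correct the label, state the 12-month rate actually assumed, and restate the power for it, saying whether the effect is held as a difference or as a ratio.
3. The quality-of-life calculation later in section 13.2.3 uses the same ED estimates, so any change of rate should be carried through to it.

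The cost is text and a short recalculation, with no added patients or visits. Moving the comparison to the 24-month questionnaire, which is already collected, is not required. It would change the one-year comparison set in section 13.4.4, and the protocol gives no 24-month compliance figure on which to judge it.

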### 13.2.4 Quality-Adjusted Survival

The SQLI generates a maximum of 125 health states. The utilities for these health states has been obtained by Weeks et al. The SQLI will be assessed prior to the start of therapy, at 6, 9, 12, 18, and 24 months, then every six months through year five. The utility will then be multiplied by the duration in a health state, which will produce the quality-adjusted survival over the first five years. Patients will be assumed to be in a health state until a change in status is noted. An effect size of 0.20 will be examined with 90% statistical power and 0.05 (*two-sided*) level of significance.

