| Lymph node assessment                                       | X b           |                  |                          |                                |   |   |    |    |    |    |                 |
| Radionuclide bone scan k                         | X c           |                  |                          |                                |   |   |    |    |    |    |                 |
| Digital examination                                         | X                        |                  |                          | X                              | X | X | X  | X  | X  | X  | X               |
| Urethrogram                                                 | X d           |                  |                          |                                |   |   |    |    |    |    |                 |
| Toxicity Evaluation                                         |                          | X                |                          | X                              | X | X | X  | X  | X  | X  | X               |
| PA and Lateral chest x-rays                                 | X c           |                  |                          |                                |   |   |    |    |    |    |                 |
| Tissue for banking                                          | Recommended              |                  |                          |                                |   |   |    |    |    |    |                 |
| Blood for banking                                           | Recommended l |                  | Recommended l |                                |   |   |    |    |    |    |                 |
| International Index of Erectile Function Questionnaire [PQ] | X                        |                  |                          |                                | X |   | X  |    |    |    | X i  |
| Functional Alterations due to Changes in Elimination [FA]   | X                        |                  |                          | X                              | X | X | X  |    | X  |    | X h  |
| Spitzer Quality of Life Index [SP]                          | X                        |                  |                          | X                              | X | X | X  |    | X  |    | X h  |

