- 11.4.3 The Spitzer Quality of Life Index (SQLI) [SP]** is a five item categorical questionnaire with three item response options scored from 0-2 and summed in a Likert format with total scores ranging from 0-10. The reliability and validity have been established. The SQLI has been criticized because it does not assess symptoms, which is the reason for pairing it with the patient self-assessment of skin reactions. The SQLI has been used in testicular patients, gastric patients, terminal patients, glioma patients, lung, ovary, and breast cancer patients The SQLI has been applied as both a rater-assessed form and a patient self-assessment form. We will be using the SQLI as a patient self-assessment form. In addition to providing a global measure of quality of life, researchers have developed a conversion factor that uses the SQLI data to produce utilities. The utilities derived from the SQLI will be used to analyze quality-adjusted survival within the first five years on study. SQLI is assessed every six months in order to document transitions in health states for quality-adjusted survival.

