| Radiotherapy Form (T1)                                             | Within 1 wk from end of RT                                                                                                          |
| (Copy to RTOG HQ and ITC)                                   |                                                                                                                                     |
| 
Initial Follow-up Form (FS)                                    | 
90 days from start of treatment                                                                                                 |
| Functional Alterations due to
Changes in Elimination [FA]       |                                                                                                                                     |
| The Spitzer Quality of Life Index [SP]                             |                                                                                                                                     |
| 
Follow-up Form (F1)                                            | 
6, 9, 12 months in year 1; q 3 months in year 2; q 6 months x 3 years, then annually; Also at progression/relapse and at death. |
| 
International Index of
Erectile Function Questionnaire [PQ] | 
6 and 12 months from start of treatment; then annually through year 5                                                           |
| 
Functional Alterations due to
Changes in Elimination [FA]   | 
6, 9, 12, 18, and 24 months; then every 6 months through year 5                                                                 |
| The Spitzer Quality of Life Index [SP]                             |                                                                                                                                     |
| 
Autopsy Report (D3)                                            | 
As applicable                                                                                                                   |

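### Quality-adjusted survival holds the last reported health state with no limit for unreturned forms, and its SQLI schedule leaves out the 3-month form that the protocol collects

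*Protocol*

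**What the plan says.** **The rule.** Section 13.2.4 converts the SQLI to utilities and defines the endpoint: "The utility will then be multiplied by the duration in a health state, which will produce the quality-adjusted survival over the first five years". The next sentence fixes how long a state lasts: "Patients will be assumed to be in a health state until a change in status is noted". Nothing in the section separates a state that has not changed from a form that was not returned, and it does not say how death enters. Section 13.4.4 compares the average between arms with a z-test.

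**The schedule.** Three versions stand in the protocol:

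- 13.2.4: "The SQLI will be assessed prior to the start of therapy, at 6, 9, 12, 18, and 24 months", then six-monthly to year 5. There is no month 3.
- 11.1 and 12.1: the calendar marks the SQLI at 3 months, and 12.1 lists it with the initial follow-up form, due "90 days from start of treatment".
- 11.4.3: "SQLI is assessed every six months in order to document transitions in health states for quality-adjusted survival".

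**The purpose.** Section 1.7 expects a difference in symptom control or toxicity to show in five-year quality-adjusted survival. Sections 6.12.3 and 11.5.1 define acute toxicity as the first 90 days from the start of radiotherapy.

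**The concern.** A rule that holds a state until a change is reported is an ordinary step function while forms keep arriving. Once they stop, the same words become open-ended carry-forward: the last utility runs to year 5. A patient with only a baseline form would have all 60 months valued at his pre-treatment state.

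The omission of month 3 adds to this. With month 6 as the first form after baseline, the baseline utility spans the full course and the acute period. An acute loss that resolves by month 6 then leaves no trace in an endpoint meant to register toxicity, although a form near the end of the acute window has been collected. What is at stake is whether this secondary endpoint measures what section 1.7 says it should.

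**Working it through.** **1. The plan's own power figure.** Inputs from 13.2.4: effect size 0.20, 90% power, two-sided 0.05. Per arm, n = 2(1.960 + 1.282)² / 0.20² = 526. From 13.2.2, 1410 patients give 705 per arm if split equally. Power = Φ(0.20·√(n/2) − 1.96):

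| Patients per arm | Power |
|---|---|
| 705 | 96.4% |
| 564 (80% of 705) | 91.9% |
| 526 | 90% |

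The 80% is borrowed from the erectile-function calculation in 13.2.3, since 13.2.4 gives no compliance figure. The stated 90% is reached with 526/705 = 75% of patients contributing, so it is not in error.

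**2. What the rule covers.**

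- The courses last 39/5 = 7.8 and 44/5 = 8.8 weeks, and the acute window is 90 days. Both lie inside months 0 to 6, which 13.2.4 values at baseline: 6/60 = 10% of the five years.
- Last form at month 12: (60 − 12)/60 = 48/60 = 80% of the window rests on one utility, unless death or another change is noted.

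**3. Illustration of an acute dip.** The documents give no utilities or standard deviation, so a baseline utility of 0.90 is assumed (5 × 0.90 = 4.50 quality-adjusted years). A dip d lasting to month 3 costs d × 3/12.

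| Dip | True value | 13.2.4 as written | Same rule plus 3-month form |
|---|---|---|---|
| 0.05 | 4.4875 | 4.500 | 4.4875 |
| 0.10 | 4.475 | 4.500 | 4.475 |
| 0.20 | 4.450 | 4.500 | 4.450 |

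The match in the last column is a coincidence of spacing: months 0 to 3 are still valued at baseline, and the month-3 state is charged to months 3 to 6. If a 0.10 dip lasts almost to month 6, the true value is 4.451 and adding the form gives 4.475, about half of the loss. Linear interpolation gives the same total here (½ × 6/12 × 0.10 = 0.025), so it is the extra form that recovers the acute signal. Interpolation helps with lasting changes. Forward holding dates each change at the form that reports it, so with six-month spacing a lasting fall is registered on average 3 months late. For a fall of 0.10 that is 0.10 × 3/12 = 0.025 years.

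**4. Illustration of stopped forms.** Last form at month 12, and utility falls by d from month 24 (a loss of d × 36/12):

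| Fall | True value | Credited | Overstatement |
|---|---|---|---|
| 0.05 | 4.35 | 4.50 | 0.15 |
| 0.10 | 4.20 | 4.50 | 0.30 |
| 0.20 | 3.90 | 4.50 | 0.60 |

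With every form returned, the same rule gives the true value in each row, so the error comes from the unreturned forms alone.

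The error can also run the other way. If the last form is at month 6 with utility 0.10 down, and the patient recovers by month 9, the rule charges the loss to month 60: an understatement of 0.10 × 51/12 = 0.425 years.

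**The case against.** The strongest reply is that the hold-until-change sentence says nothing about missing data. It follows the utility-times-duration definition and may only explain how states between visits become durations, with unreturned forms left to an analysis plan that is not shown. The month-3 gap may likewise be a slip: the 13.2.4 list matches the later row of 12.1, no text excludes the collected form, and a change noted on it would end the baseline state.

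The stake is also modest. A 0.10 dip to month 3 costs 0.025 of 4.50 quality-adjusted years, and equal dips in both arms largely cancel. Section 11.4.3 concedes that the SQLI does not assess symptoms. Acute toxicity is graded weekly, and bowel and bladder symptoms have FACE, collected at month 3, with its own area-under-the-curve analysis.

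Much of this stands and limits the point to a secondary endpoint with a cheap remedy. It does not remove it. The protocol itself states the rule and gives it no end, so an analyst who follows it carries states to year 5. Three schedules also leave it unclear which forms enter the calculation.

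**Conclusion.** The point holds as a defect in a stated rule plus an internal contradiction. As written, 13.2.4 values months 0 to 6 at baseline and allows 48 of 60 months to rest on a 12-month form. The amounts in quality-adjusted years depend on the assumed utilities. Death is taken to count as a noted change, so the over- or under-crediting concerns living patients who stop returning forms.

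A reader might infer more, but the documents do not support it:

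- *That the protocol expects 20% of SQLI forms to be missing.* The "80% compliance at 1 year" belongs to the erectile-function calculation. Missing one 12-month form also differs from returning none after baseline.
- *That power falls to 85% or 75%.* Those values come from shrinking 0.20 to 0.16 or 0.14 at 705 per arm. That requires 20% or 30% of patients to contribute no arm difference for five years. The undiluted comparator at 705 is 96%; the stated 90% needs only 526.
- *That the arms are necessarily pulled together.* Step 4 of the working shows errors in both directions. The net effect depends on differential toxicity and non-response, for which no figures are given.
- *That the standard error is too small.* The z-test uses one total per patient. Whether holding a value narrows or widens the spread of totals depends on correlations between visits that are not stated.

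**What to change.** - Align 13.2.4 and 11.4.3 with 11.1 and 12.1, and state that the 3-month SQLI enters the calculation.
- Value the time between returned forms by linear interpolation (or a stated midpoint rule), with death as zero.
- Do not carry a state past the next scheduled form when that form is missing. Use multiple imputation or inverse-probability-of-censoring weights, and name the method.
- Keep the present carry-forward rule as a sensitivity analysis.

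The cost is analysis wording and a little programming, with no new data. The main analysis would then rest on a missing-at-random type of assumption, which should be stated.
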